**Fig. 1 Fig1:**
[figure not shown]
Flowchart of the study protocol from contact companies to data analysis (LG = live workshop group). Participants receive a reminder via email

The study lasts about six months for each group. Each workshop and measurement for data collection is promoted by the institutions’ health counselor. Our workshop address three important components for office workers’ health promotion: organizational (i.e. structures, health services), workplace (i.e. equipment, premises), and individual (i.e. health behavior, motivation) components. Details of our intervention are described below. Besides the two interventions groups participants of the control group will receive the pre- and post-study questionnaire.

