The participation should motivate and offer new perspectives of increasing physical activity at the workplace. We have also designed the workshop in such a way that our concept can be used in various companies. In this first step, we want to prove our concept in medium-sized organizations. Due to the current pandemic situation, there is an increasing number of people working in separate offices without any contact with other co-workers. To ensure that these changes do not lead to increased inactivity, new work-related health offers or activity programs should be established. We developed a workshop which takes all the above-mentioned points into account. The use of computer prompts combined with providing information reduces sitting time on average by 14 to 96 min per day*.* In this early stage, we want to prove the concept of our live approach in small groups and hypothesize that the participants show positive health effects (i.e. well-being, decreased MSD) and positive adaptations in their health behavior (i.e. increased physical activity). We hypothesize that additional reminders improve health-related effects. In addition, we want to develop our workshop design in the framework of eHealth applications or a web-based solution, since the integration of such approaches might improve the efficiency of health programs at work [37].

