## Methods

### Participants

We recruit office desk workers aged between 18 and 67 years from different organizations (i.e. public administration with standard office workplaces) in Germany. Two intervention lines are planned: one live workshop group with and one without reminders. After attending the first workshop participants in the appropriate intervention group will receive reminders via e-mail twice a week. The e-mails remind the participants of the possibilities to be physical active at the work place previously introduced through the workshop. Overall, eight e-mails will be sent until participants answer the second online survey one month after participating in the workshop. We use a randomized allocation of the participants to both groups. As inclusion criteria, we define an age group between 18 and 67 years and the employee council of each institution has to approve the participation. Additionally, participants are asked not to take part in other studies during the time of the workshop intervention. Participants are excluded if they take part in only one workshop or do not fill in the questionnaires (missing answers > 30%) appropriately. All participants will be informed about the content and objectives of our study, they can ask questions, and they can withdraw from the participation at any time. As a prerequisite for participation, participants of our study sign a declaration of consent. A meta-analysis [38] revealed small intervention effects of workplace physical activity interventions (d = 0.21). Based on this assumption, power-analysis (G-Power 3.1) indicated in sum 168 participants for an ANOVA with repeated measures (within-between interaction). Our calculation included *f* = 0.11, *α* = 0.05, β = .80, three groups, and three measurements.

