## Discussion

We introduced a workshop to increase health-seeking behaviors in office workplaces in Germany. Our workshop is based on a combination of physical activity and health behavior planning.

At first, we want to indicate one minor limitation regarding our data acquisition: we have to validate our PAD. The diary is adapted to a validated questionnaire; however, that questionnaire has not been validated for daily usage. Moreover, the literature showed differences between self-reported (i.e. by questionnaires) and accelerometer-measured physical activity [48, 49]. Therefore, we use accelerometer-measured physical activity to prove our PAD in a sub-sample of our participants. If the result of our analysis shows insufficient validity, only the data from the accelerometry will be used. Another limitation refers to the recruitment process. The participants are recruited in different organizations and therefore have different pre-conditions (i.e. workplace equipment, health services) as well as differently effective health counsellors. Thus, we will collect data on the organization to control for potential experimenter effects between organizations.

In addition, there is some risk of inter-subject group bias if individuals in one group inform a member of the other group about reminders. In the follow-up survey, we will ask the group without reminders whether they received information about the procedure in the other group. We can then perform analyses according to whether participants received information about the other group and exclude them from the analyses, where necessary. Participants of the workshops might be less active in winter. Hence, the season could affect the amount of physical activity. As data of both intervention groups will be collected in the same season, they remain comparable. All these issues could affect our results and should be critically reviewed later.

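### The 168 participants are calculated for three groups measured three times, but the control group is described with two questionnaire occasions and outside the stated randomisation, so the stated 80% power belongs to a different design

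*Protocol article*

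**What the plan says.** All references are to the Protocol article.

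- **Sample size (Methods, Participants).** The power analysis "indicated in sum 168 participants for an ANOVA with repeated measures (within-between interaction"). The inputs are "Our calculation included *f* = 0.11, *α* = 0.05", a value of .80 labelled β, and "three groups, and three measurements". The effect size comes from a meta-analysis that "revealed small intervention effects of workplace physical activity interventions (d = 0.21").
- **Randomisation (Methods, Participants).** Two intervention lines are described, one workshop with and one without reminders, and then: "We use a randomized allocation of the participants to both groups". The Abstract likewise describes a randomised trial with two intervention groups.
- **Control group (Methods, Study-aim and procedure, after Fig. 1).** "Besides the two interventions groups participants of the control group will receive the pre- and post-study questionnaire". The text does not say how this group is recruited or allocated.
- **Measurements (Methods, Study-aim and procedure).** Questionnaire, diary and accelerometer are scheduled in the week before the first workshop, again in the week before the refresher, and at six months. The same paragraph sends devices and diaries to everyone who has consented.
- **Instruments (Methods, Measurements).** The online questionnaire holds the musculoskeletal, well-being and HAPA instruments. The activity diary and the accelerometer are separate.
- **Hypotheses (Introduction).** The authors "hypothesize that the participants show positive health effects (i.e. well-being, decreased MSD) and positive adaptations in their health behavior (i.e. increased physical activity"), and separately expect reminders to add to the health-related effects.
- **Season (Discussion).** Season is named as a possible influence on activity, with the answer: "As data of both intervention groups will be collected in the same season, they remain comparable".

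**The concern.** The sample size rests on a complete grid of three groups by three occasions. As the control group is described, one cell of that grid is empty: the middle measurement is tied to the refresher workshop, and controls are given a pre- and a post-study questionnaire. The 80% power then belongs to a test that the described data cannot fill.

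Two further things are at stake for the first hypothesis, that workshop participants become healthier and more active.

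- The stated scope of randomisation is the two workshop groups. A workshop-versus-control comparison would not have the protection that the reminder comparison has.
- If controls contribute no diary or accelerometer data, the workshop effect on activity is a change from baseline to about 24 weeks later without a comparator. The article itself says that season may affect activity, and the two time points lie about half a year apart.

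**Working it through.** **Inputs.** From Methods, Participants: f = 0.11 (d/2 = 0.21/2 = 0.105, rounded up), α = 0.05, target 0.80 (read as power, although it is labelled β), k = 3 groups, m = 3 measurements, total N = 168. The correlation among repeated measures (ρ) and the nonsphericity correction (ε) are not stated. I assume ρ = 0.5 and ε = 1, and show ρ from 0.3 to 0.7.

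**Formula** (within-between interaction, noncentral F):

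- λ = f² × N × m × ε / (1 − ρ)
- df1 = (k − 1)(m − 1)ε; df2 = (N − k)(m − 1)ε
- power = P(F′(df1, df2, λ) > F(0.95; df1, df2)), with N in multiples of k

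**Step 1: reproduce the plan's figure (3 × 3).** λ = 0.0121 × 168 × 3 / 0.5 = 12.197; df1 = 4; df2 = 165 × 2 = 330. Power = 0.803. At N = 165 it is 0.795, so 168 is the smallest multiple of three that reaches 80%. The plan's figure is reproduced exactly, which supports the assumed ρ and ε.

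**Step 2: three groups, two occasions (questionnaire outcomes with controls).** λ = 0.0121 × 168 × 2 / 0.5 = 8.131; df1 = 2; df2 = 165. Power = 0.717. For 80% power N = 204 (λ = 9.874, power 0.804).

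**Step 3: two workshop groups, three occasions (no controls).** The article does not give the group sizes.

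- Equal split assumed: 168 × 2/3 = 112 in the workshop groups. λ = 0.0121 × 112 × 3 / 0.5 = 8.131; df1 = 2; df2 = 220. Power = 0.719.
- All 168 in the workshop groups: λ = 12.197; df1 = 2; df2 = 332. Power = 0.886.
- N for 80% power is 136.

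**Step 4: dependence on the assumed correlation.**

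| Design | ρ = 0.3 | ρ = 0.5 | ρ = 0.7 |
|---|---|---|---|
| 3 × 3, power at 168 | 64% | 80% | 96% |
| 3 × 2, power at 168 | 56% | 72% | 91% |
| 3 × 2, N for 80% | 282 | 204 | 123 |
| 2 × 3, N for 80% | 188 | 136 | 82 |

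At each of these correlations the 3 × 2 design has less power at 168 than the 3 × 3 design. From ρ of about 0.59 upward, 168 is enough for 3 × 2 as well.

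**Step 5: the season argument.** It compares the two intervention groups with each other at the same time of year, which protects reminders versus no reminders. It does not protect a comparison of the same people at baseline and about 24 weeks later. The size of a seasonal shift cannot be worked out from the article.

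**The case against.** - **The control sentence does not say that controls receive nothing else.** Study-aim and procedure sends accelerometers and diaries to everyone who has consented, and Fig. 1 is not available here. This stands in part. A reader might infer that no control activity data will exist, but the text does not establish that. The paragraph in question is, however, built around people who choose a workshop date, with timing set by their first workshop. The two statements therefore have to be reconciled.
- **The Statistics section does not commit to a 3 × 3 ANOVA.** It speaks only of analyses for repeated measurements. This stands. A reader might infer that the planned analysis cannot be run at all, but that goes too far. A 3 × 2 analysis of questionnaire scores, a 2 × 3 analysis of the workshop groups, or a mixed model with unequal numbers of occasions all remain possible. What fails is the match between the sizing design and the described data.
- **The article nowhere calls workshop versus control randomised.** This stands. It is also tempting to say that controls select themselves, but the article does not say how controls are formed, so only the absence of a described random allocation can be asserted.
- **The 72% rests on an unstated correlation.** This stands, and for that reason it is given with its range.
- **Season is already named as a limitation.** It is, but the reassurance offered covers only the comparison between the two workshop groups.

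**Conclusion.** The point holds as a mismatch between the design that was sized and the design that is described. The arithmetic behind 168 is right for three groups by three occasions. The text delivers two randomised workshop groups with three occasions, and a control group with two named questionnaire occasions and no described random allocation.

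Under f = 0.11, ρ = 0.5 and ε = 1 (the last two assumed), power falls from 80% to 72% for the three-group questionnaire comparison. For the two workshop groups alone it is between 72% and 89%, depending on how many of the 168 they hold.

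The consequence for the physical activity hypothesis is conditional. If controls provide no diary or accelerometer data, a before-after change in activity cannot be separated from season. The reminder comparison keeps its randomisation and its protection against season. The article says that the study has not started, so the missing measurements can still be arranged.

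**What to change.** 1. **Control group measurements.** State which instruments the control group receives and on which occasions, so that the two statements in Study-aim and procedure agree. Send controls the online questionnaire and the diary at the middle measurement, and the diary at the other two, so that all three groups have three occasions and the 3 × 3 calculation applies. If controls stay at two occasions, restate the power for the design delivered: 3 × 2, about 72% at N = 168 with ρ = 0.5, with the range 56% to 91% for ρ from 0.3 to 0.7. State the assumed correlation in either case.
2. **Status of the comparisons.** State that only reminders versus no reminders is randomised and confirmatory. Label workshop versus control as non-randomised and exploratory, adjusted for baseline, company and calendar month.
3. **Reading of activity change.** State that an uncontrolled before-after change in diary or accelerometer activity will not be read as a workshop effect. If controls receive the diary but no accelerometer, this still applies to the accelerometer data.

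The cost is a little more survey and diary work for controls, some protocol wording, and a weaker claim for the workshop effect.

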### Intervention

The first workshop lasts about two hours, the refresher workshop only one hour. Each workshop consists of active and passive parts. Table 1 describes the first workshop including active and passive parts. The refresher workshop includes some new activities (see part III in Table 1) as well as an interactive question-answer part. In the latter participants can ask questions about the workshop and further individual strategies, and can discuss adaptations. This concept is used in a live workshop with and without reminders. The reminders are used to retain the acquired contents and knowledge of the first workshop and to give incentives for physical activity.

**Table 1 Tab1:** Description of main contents during the workshop; participants were actively (i.e. physically active) or passively involved

***Part***	***Content***	***Participants’ involvement***
I	Workshop trainers give some general information about inactive lifestyle and behavior (i.e. statistics) at German workplaces and resulting health-related issues (i.e. physically, social, psychological), based on recent studies. Different concepts for increased physical activities at the workplace are shown and participants are asked in anonymized live-questions about their daily physical activity.	passive
II	The trainers give instructions on adequate health safety standards regarding the office desk setting, based on German laws and regulations. This includes the rights & duties as well as the health-related behavior of office workers at their workplace (i.e. position of the desk, equipment, sitting/standing positions) in Germany. Again, the participants are asked for their participation in anonymized live-questions about these topics.	passive
III	Trainers show some exercises from the areas of mobilization, strengthening, and stretching. All examples can be performed at the workplace. At the end of this tryout, some recommendations for physical activity (i.e. how long and often exercises should be performed) are given.	active
IV	Trainers and participants of the workshop discuss opportunities and barriers to daily physical activity in individual group activities. Experiences are shared and the group works on the conception of action plans. Finally, each participant should create his/her plan.	active

The live workshops take place according to the current hygiene guidelines (i.e. visit https://www.infektionsschutz.de/coronavirus/). These guidelines currently recommend a minimum interpersonal distance of 1.5 m, wearing a personal protective equipment such as a face mask, and good hygiene practices including hand washing etc., (including hand washing for at least 20 s, avoiding touching each other, sneezing into the elbow, etc.). Moreover, further precautionary arrangements are made, for example, smaller size groups, large rooms for sufficient interpersonal distance, regular airing, and disinfection of all tools that are used.

### Measurements

In the first step, we conduct a structured telephone interview with the health counselor from the company. The respective manual will be attached as supplementary material (S1). The aim is, to explore health offerings, courses, and general attitudes towards employees’ health, health promotion, and programs. Subsequently, small discussion parts of our workshop will be adapted to the company’s framework (i.e. if offices have no height-adjustable desks, we won’t discuss it). Using this approach, we create a crucial prerequisite for multilevel interventions at the workplace: the inclusion of the organization [13].

The subsequently described questionnaires (i.e. Nordic Musculoskeletal Questionnaire, Questionnaire of physical well-being, and Health Action Process Approach) are embedded in one online questionnaire that was built using LimeSurvey, an open-source online survey tool. In compliance with the “*Datenschutz Grundverordnung*” (DSGVO), we hosted the survey on an internal server from the Charité – Universitätsmedizin Berlin, and participants get an email-link for participation.

#### Nordic musculoskeletal questionnaire (NMQ)

This questionnaire aims to detect musculoskeletal stress in different regions of the body [40]. The NMQ consists of two parts: first, general information about the participant including the individual situation at work, and second, detailed questions about previous and existing physical stress. The latter also examines special regions of the body (i.e. neck, shoulder, lower back). All questions include the duration and frequency of physical stress, especially during the last 12 months and the last seven days. Previous research concluded that the NMQ is sensitive, repeatable, and a useful screening tool [41]. We use this questionnaire in two ways: (i) as a screening tool to adapt the physical activities in our refresher-workshop, and (ii) to record changes in physical stress a few weeks after the workshop.

#### Questionnaire of physical well-being (FEW-16)

The FEW-16 contains some statements about the body, physical capacity, and relaxing. It is a retrospective assessment of the general situation during the last three weeks. Therefore, participants have to indicate the extent to which they agree with the individual statements. The questionnaire contains four scales each includes four items (i.e. stress resistance, ability to enjoy, vitality, and inner peace). Each item is assessed by a six-point Likert scale with a range from zero: “not applicable at all” to five: “fully applicable”. Kolip and Schmidt (1999) reported high internal consistencies (i.e. α = .82 to .92) for the total scale and the subscales and validated the questionnaire with questionnaires on quality of life and functional impairments [42]. Although the FEW-16 contains four scales, in a non-clinical context the physical well-being seems to be one-dimensional [43]. Thus, in our study, we will use the sum-score of all sub-scales. The score ranges from zero to 80 points, in which higher scores represent higher well-being.

#### Health action process approach (HAPA)

The HAPA model (Fig. 2) assumes health behavior as a process with at least two stages: motivation and volition [28, 29]. The first stage includes individuals’ risk perception, outcome expectancies, and task self-efficacy, and results in a formed intention. The latter stage includes planning, execution, and maintenance of health behavior, and leads to actual behavior change. The HAPA model was proven in some empirical studies [29]. The author reported that especially the improvement of action planning and coping planning in patients motivated to increase their physical activity. The questionnaire as well as further information can be received from *http://userpage.fu-berlin.de/%7Ehealth/hapa.htm*.

**Fig. 2 Fig2:**
[figure not shown]
HAPA-model by Schwarzer R. (adapted from Schwarzer, 2008)

The questionnaire contains different subscales (i.e. self-efficacy, planning, intention, outcome expectations, and risk perception). Subscale items are assessed by a four-point Likert scale (i.e. from zero = “not applicable at all” to three: “fully applicable”), except the risk perception with a five-point Likert scale. Scores are computed by adding or averaging the answers over all items.

#### Physical activity diary (PAD)

The physical activity diary is adapted to the German-PAQ-50+ [44], which is a retrospective assessment of one month of daily physical activity. Huy and Schneider (2008) reported acceptable reliability but did not validate the questionnaire as the PAQ-50+ consists of two already validated questionnaires (i.e. YPAS and PASE) [40]. We use the PAQ-50+ in our physical activity diary to assess daily physical activity. Answers are given in hours/week and are added to a sum-score that is multiplied by an appropriate energy score (i.e. MET-value).

#### Activity tracker

Physical activity is objectively measured by ActivPAL™ (PAL Technologies), which is a validated and reliable accelerometer for activities like sitting, standing, or walking [45, 46]. Especially in sedentary behavior, the ActivPAL™ is a precise and sensitive measurement tool [47]. The sensor is attached to the right thigh and measures not only the number of steps but also various activity patterns. In this study, the measurement is performed over seven consecutive days to examine the average physical activity and to have a comparative value to the PAD.

### Statistics

All data are processed to enhance quality; for example, in case of missing data, we conduct a missing value analysis (MVA) with a subsequent imputation procedure. Outliers are checked manually. Then, it is planned to perform analyses for repeated measurements of physical wellbeing, HAPA subscales, and the results from the physical activity diary. Results from the Nordic Musculoskeletal Questionnaire are analyzed descriptively. For all analyses, the significance level is set to 0.05.

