**Methods:**

We use a randomized controlled trial with two intervention groups: a live workshop with and without additional reminders. The workshop intervention design consists of a baseline measurement, two workshops, and one follow-up measurement. Each workshop takes place in small groups (*n* < 11). We use a randomized allocation to both groups. To control for health-related effects and the expected behavior change we examine (i) physical activity (i.e. active time, taken steps, etc.) by a tracking device (ii) physical wellbeing, motivation, and volition by an online questionnaire, and (iii) participants also report physical activity by a diary. All measurements are taken one week before the respective workshop and 24 weeks after the initial baseline measures.

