### Study-aim and procedure

Our study aims to examine health-related effects from two slightly different live workshops with office workers. Therefore, we contact health counselors at various companies in Germany. If they are interested in participating in our study, further details will be discussed and the employee council and management level will be involved. If the management approves our study, the health counselors will be interviewed and will help to distribute the information among the employees (i.e. via email). In an email, participation in one of our groups will be clearly explained. The study information and the consent form are attached to this email, with additional contact details of the study supervisors (i.e. regarding upcoming questions). As a prerequisite for participation, these documents must be signed and returned. The participants have the opportunity to choose a suitable date from a list of workshop dates in their company. Each participant receives a link to participate in the online questionnaire as well as an activity diary one week before their first workshop. Additionally, we use accelerometers to objectively measure physical activity during this week. Accelerometers with instructions, activity diaries and an online survey will be sent to all consenting participants for data collection. The instructions explain how to attach the accelerometer to the participant’s thigh and hip. Previous studies have indicated three days are sufficient to observe a stable pattern of physical activity [39]. Not wearing the accelerometer for 3 successive days leads to exclusion of the participant from the study.

This procedure is repeated one week before the refresher workshop and after six months. We have no blinding of our workshop supervisors and outcome assessors or data analysts. In each group data collection starts one week before the first workshop. The study procedure is presented in Fig. 1.

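### The planned analyses name the diary but no accelerometer outcome, and the rule for switching between the two has no criterion

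*Protocol article*

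**What the plan says.** The abstract's Methods paragraph lists first, among the measures for health effects and behaviour change, "physical activity (i.e. active time, taken steps, etc.) by a tracking device". The Introduction hypothesises increased physical activity. The Activity tracker section states that "Physical activity is objectively measured by ActivPAL™ (PAL Technologies), which is a validated and reliable accelerometer", worn for seven consecutive days to obtain average activity and a comparator for the diary. Under Study-aim and procedure, "Accelerometers with instructions, activity diaries and an online survey will be sent to all consenting participants for data collection", and a participant who leaves the device off for three days in a row is excluded.

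The Statistics section gives the list of analyses: "it is planned to perform analyses for repeated measurements of physical wellbeing, HAPA subscales, and the results from the physical activity diary". It adds that the musculoskeletal questionnaire is analysed descriptively. The accelerometer does not appear.

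The Discussion says that the diary still has to be validated, because its parent questionnaire was not validated for daily use, and that self-report and accelerometry are known to differ. It continues: "we use accelerometer-measured physical activity to prove our PAD in a sub-sample of our participants". The consequence is then set: "If the result of our analysis shows insufficient validity, only the data from the accelerometry will be used". Study-aim and procedure states that workshop supervisors, outcome assessors and data analysts are not blinded. The same section mentions only questionnaires before and after the study for the control group.

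**The concern.** The trial sets out to show a change in physical activity and collects an objective measure of it. The one list of planned analyses uses the self-report instrument instead, which the article itself treats as not yet validated. Accelerometry becomes the sole source of the activity result only through a check on the trial's own data, and the reader cannot tell in advance what would count as failing it.

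Two things are at stake. First, the headline activity result may come from the measure more open to reporting error, while the better measure has no stated analysis. Second, an unblinded analyst could settle which measure counts after seeing the group comparison on both. Under Monitoring and ethics, the article relies on advance publication to make later changes traceable. A switch without a criterion weakens that protection, because either choice would be consistent with the published plan.

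**Working it through.** **1. The sections side by side**

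| Section | Role of the accelerometer | Role of the diary |
|---|---|---|
| Abstract, Methods | first-listed measure | third-listed measure |
| Study-aim and procedure | sent to all who consent; non-wear excludes | sent to all who consent |
| Activity tracker | average activity; comparator for diary | compared with device |
| Statistics | not named | repeated-measures analysis |
| Discussion | reference for validation; sole source if diary fails | to be validated; dropped if it fails |

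The Statistics section gives even the musculoskeletal questionnaire a role (descriptive), so the absence of the device stands out.

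**2. The plan's own sample size**

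Inputs from the Participants section: f = 0.11, alpha = 0.05, power 0.80 (printed as beta), k = 3 groups, m = 3 measurements. The article gives neither the correlation between measurements nor a sphericity correction; rho = 0.5 and epsilon = 1 are assumed.

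- Noncentrality: f² × N × m / (1 − rho) = 0.0121 × 168 × 3 / 0.5 = 12.20.
- Degrees of freedom: (k − 1)(m − 1) = 4 and (N − k)(m − 1) = 330.
- Power at N = 168 is 0.803. The exact minimum is 167, or 168 with three equal groups.

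The stated 168 is reproduced. With rho from 0.3 to 0.7 the same inputs need 234 down to 102. The calculation is not tied to a particular outcome, so naming the accelerometer does not by itself change it.

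**3. What the switch can do to the type I error**

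This was simulated with no true group effect: 20,000 runs, 168 / 3 = 56 per arm, and one two-sample comparison at two-sided 0.05. Diary and accelerometer were given an assumed correlation r. Under the validity-only rule, the diary is kept if the observed correlation reaches a fixed cut-off (set at r, so that both branches occur often). Under free choice, the result counts as significant if either measure is.

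| Assumed r | Validity-only rule | Free choice |
|---|---|---|
| 0.2 | 0.049 | 0.097 |
| 0.4 | 0.053 | 0.097 |
| 0.6 | 0.050 | 0.085 |

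The simulation standard error at 0.05 is √(0.05 × 0.95 / 20,000) = 0.0015. The upper bound for two independent measures is 1 − 0.95² = 0.0975. The simulation assumes that neither measure is biased by arm; the documents give nothing from which to size such bias.

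**4. Power if the contrast is narrowed to reminders versus none**

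With 56 per arm and the article's d = 0.21, the noncentrality of a simple two-arm test is 0.21 × √(56 / 2) = 1.11, and power is about 20%. With baseline adjustment the noncentrality is divided by √(1 − r²), where r is now the baseline-to-follow-up correlation. Power is then about 25% at an assumed r of 0.5 and 34% at 0.7.

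**The case against.** The strongest reply is that the Statistics section is a short passage in a condensed article and that its list is incomplete, not exclusive. Accelerometry clearly has a place in the design: it has its own stated purpose, non-wear leads to exclusion, and saying that it alone will be used if the diary fails suggests that it is used alongside the diary otherwise. The switch depends on agreement between the instruments, not on arm results, and it moves towards the objective measure. A cut-off and its timing could stand in an analysis plan that is not shown.

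Part of this stands. The device is not unused, and the rule as worded does not in itself inflate the type I error. The reply does not remove the conflict, however. The article chose to list its repeated-measures outcomes and to publish a switching rule. The list disagrees with the Abstract and the Activity tracker section, and the rule cannot be applied as published.

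Four stronger readings are tempting and are not supported:

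- A reader might infer that only some participants wear the device, so that a switch would cost precision. The Discussion says that the diary is validated in a sub-sample. That is compatible with everyone who consents wearing the device.
- A reader might infer that participants are unblinded and that diary bias by arm is therefore established. The article names supervisors, assessors and analysts as unblinded, not participants. It treats leakage of information about the reminders as a risk, which suggests that the group without reminders is not meant to know. Differential reporting is plausible but not documented.
- A reader might infer from "For all analyses, the significance level is set to 0.05" that a chance finding is likely. For seven scales (wellbeing, five named HAPA subscales, diary) the chance of at least one is 5% if fully correlated and at most 1 − 0.95⁷ = 30% if independent. A multiplicity method may also be left to the analysis plan.
- A reader might infer that the switch necessarily inflates error. The simulation shows that it does so only when the choice follows the results.

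**Conclusion.** The concern holds in this form: the stated analyses omit the objective activity outcome that the rest of the article presents as central, and the move from diary to accelerometry is left to an undefined check on trial data by unblinded analysts. The consequence for error is conditional. It is about 0.05 under a fixed validity rule and about 0.085 to 0.097 if the favourable measure is freely chosen, for assumed correlations of 0.6 to 0.2, 56 per arm and a single two-arm comparison. Nothing in the article says that such a choice is intended; the point is that nothing in it prevents one. The larger matter is which measure carries the activity conclusion. That rests on the text alone and on no assumption about correlation.

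**What to change.** 1. In Statistics, name one ActivPAL outcome (for example mean daily steps or active time) as the physical activity outcome. Analyse it in all participants who receive the device, with the repeated-measures group-by-time analysis and baseline taken into account.
2. Make the diary secondary whatever its validation shows.
3. Delete the switching rule in the Discussion. If it is kept, fix the agreement statistic, the cut-off, the sub-sample and the time point, and complete the check before any group comparison.
4. Clarify in the Discussion that the sub-sample refers to the diary validation and not to who wears the device.
5. State whether the control group wears it. If it does not, the device analysis covers only the two workshop arms, and the three-group calculation does not describe it.
6. If reminders versus no reminders is made the primary contrast, restate the power. The 168 was computed for a three-group, three-measurement interaction, and a simple two-arm test at 56 per arm has about 20% power at d = 0.21.

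The Data Availability statement says that the study had not started, and the devices are already planned, so steps 1 to 5 are changes of wording. Their price is that the diary loses its standing as the activity outcome. Step 6 is not free: choosing that contrast may call for a different sample size.
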